### Study population

#### Inclusion criteria

Participants must meet all of the following criteria to be eligible for this study:

Aged ≥ 18 years.HIV-1 infection documented using FDA-approved screening and confirmatory or supplemental assays in Centers for Disease Control and Prevention (CDC)–recommended testing strategies.Established medical care outside NIH.Able to provide informed consent.Willing to allow samples to be stored for future research.Willing to allow genetic testing.Undergoing ART using recommended, alternative, or other regimens as defined by “Guidelines for the use of Antiretroviral Agents in HIV-1 infected adults and Adolescents” (65).Viral RNA < 40 copies/mL plasma by conventional assay for at least 3 years [blips (transient increases within 6 weeks) (66) of <200 copies/mL are allowable when succeeding viral levels return to <40 copies/mL on subsequent testing].CD4 cell count ≥350 cell/μL.Willing to interrupt ART for up to 90 days.Willing to use a barrier method of contraception such as condoms or dams when engaging in sexual activity, or remain abstinent during ATI and after re-initiating ART until viral re-suppression is achieved, to prevent pregnancy and transmission of HIV.

#### Exclusion criteria

Participants who meet any of the following criteria will be excluded from this study:

Active intercurrent illness or infection, including fever >38°C.Known history of initiating ART during the first year of infection with HIV. Patients will be considered to have initiated ART within 1 year of infection as defined by documented screening/confirmatory seroconversion [positive testing within 1 year of non-reactive HIV enzyme-linked immunosorbent assay (ELISA)].Pregnant.Breastfeeding.Currently undergoing therapy with drugs that, in the judgment of the investigators, may interfere with biodistribution of FDG, including prednisolone, valproate, carbamazepine, phenytoin, phenobarbital, and catecholamines.Undergoing ART that is incompatible with an ATI.Has undergone PET/CT within the last 6 months.History of poorly controlled diabetes that, in the judgment of the investigators, would prevent completion of PET/CT scan.Vaccination within the previous 4 weeks.History of ATI within the past 1 year.Has comorbid illness for that, in the judgment of the investigators, an ATI will represent elevated risk.Active opportunistic infection as defined by the Guidelines for the Prevention and Treatment of Opportunistic Infections in Adults and Adolescents with HIV (67).Significant active substance abuse or psychiatric illness that may, in the judgment of the investigator, interfere with study visits or procedures.Allergy to planned anesthetic agents that are expected to be used. For local anesthetics, this is lidocaine. For sedation, this is midazolam and fentanyl.Currently undergoing chronic systemic steroid therapy (corticosteroid nasal spray or inhaler and topical steroid use are acceptable).Contraindication to use of IV contrast.History of developing keloids.Renal impairment: HIV-related kidney disease or estimated glomerular filtration rate (eGFR) CKD-EPI equation <60 mL/min/m^2^. For individuals undergoing therapy with cobicistat or integrase strand inhibitors (INSTIs), GFR may be estimated using cystatin C or creatinine.Active or chronic hepatitis B virus infection, with detectable hepatitis B surface antigen, hepatitis B virus DNA, or both.Active hepatitis C virus infection, with detectable virus RNA.History of HIV-associated dementia or progressive multifocal leukoencephalopathy.Documented ARV drug resistance that, in the judgment of the investigator, would pose a risk of virologic failure should additional mutations develop during the study.History of cardiovascular event or at high risk of an event (e.g., atherosclerotic cardiovascular disease score >20%) (https://tools.acc.org/ascvd-risk-estimator-plus/#!/calculate/estimate/).History of AIDS-defining illness according to CDC criteria within the past 3 years (68).Hepatic impairment: alanine transaminase >2.5 × the upper limit of normal or documented history of cirrhosis (69).Any condition that, in the judgment of the investigator, contraindicates participation in this study.

### Study intervention

#### ATI

Participants randomized to ATI will halt their ART medications starting 2 weeks (±3 days) after the first imaging visit. This plan will be discussed with participants during the baseline visit. Patients will be contacted 1–3 days prior to ATI initiation. An interim history will be collected to ensure there are no new safety concerns. ATI may be delayed or canceled if there are new safety concerns. HIV plasma viral levels and CD4 counts will be monitored every week during the ATI phase. If a participant meets any of the ART restart criteria during the ATI phase, then they will discontinue ATI and restart ART. Participants who do not meet restart criteria will remain off ART and continue to be monitored weekly until they have been on ATI for 90 days, and then will restart ART.

#### Criteria to restart ART

Participants assigned to ATI will resume ART and continue the study if they meet any of the following criteria during the ATI phase:

HIV RNA > 40 copies/mL and either a confirmed >30% decline in baseline CD4 cell count or an absolute CD4 count <300 cells/mL on 2 consecutive assesements within 2 weeks.A sustained (≥4 weeks) HIV RNA level of >1,000 copies/mL.Any HIV-related symptoms or acute retroviral syndrome presenting as fever, lymphadenopathy, sore throat, rash, myalgia/arthralgia, or diarrhea not already determined by physician examination to be related to something other than HIV.Any development of HIV-specific opportunistic infections, as listed in the DHHS guidelines (clinicalinfo.hiv.gov).ART is deemed medically necessary for non-HIV-related causes.Absolute HIV RNA >100,000 copies/mL.Participant becomes pregnant.At 90 days after starting ATI, any participant who has not met criteria to end the ATI will be instructed to restart ART.Participants who are in the ATI period who trigger a withdrawal criterion (Supplementary material S2) will also resume their pre-study ART regimen.

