**Figure 1 F1:**
[figure not shown]
Study schema. ART, antiretroviral therapy; ATI, analytic treatment interruption; VL, viral load. Depicts the overall schema for participant randomization and study procedures. Participants will be randomized 1:1 to continue ART or undergo ATI. ATI participants will undergo a total of three PET/CTs with biopsy, while those who continue ART will receive two PET/CTs with biopsy.

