Lymph node tissue and bone marrow	Needle biopsy for lymph nodes, biopsy and aspirate for bone marrow	Lymph node biopsy is required, bone marrow biopsy is optional	• *In situ* hybridization, including RNAscope and DNAscope • HIV-1 viral load. HIV RNA levels will be normalized to total number of CD4 cells, quantified using CCR5 • Cell populations, flow cytometry • Immunohistochemistry • Cytokine analysis • Interferon sensitivity of replication-competent HIV recovered • Soluble markers of immune response • ARV drug levels • Genetic testing, including HLA typing • Storage for future research
Semen/vaginal fluid	Patient self-collection	Optional	• HIV RNA and DNA levels • Storage for future research

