#### ATI or continue ART phase

After the baseline imaging visit, participants will be randomized 1:1 to either continue their ART regimen or undergo ATI, to begin 2 weeks (±3 days) after baseline. This interim serves two purposes: (1) to give ATI participants time to recover so they can be biopsied from the same site again if indicated, and (2) for those on ATI who take NNRTIs, to switch to a protease inhibitor or an integrase inhibitor–based regimen to ensure that the washout period of ARV drugs is roughly equal. The study team will work with the participant's regular care team to adjust ART regimens as needed and oversee the ATI. If necessary to ensure a safe discontinuation of ART, the interval between baseline and ATI initiation may be lengthened up to 8 weeks. ATI participants will have a second set of imaging and biospecimen collection 7–13 days after starting ATI. A biopsy reviewer who is blinded to cohort assignment (ATI or continuing ART) will review the whole body PET/CT images and determine what sites to biopsy.

Participants on ATI will have weekly study visits to monitor HIV symptoms, viral load, and CD4 count. When the participant meets a restart criterion, including reaching 90 days of interruption even if no other criterion is met, they will resume their ART at the next weekly visit. This ART restart visit will include a research blood draw. As this blood draw is critical to the study goals, participants who do not return for their ART restart visit will be replaced. Participants who withdraw prior to achievement of ART resumption criteria will similarly be replaced. However, their data will be kept as it can be used in the PET/CT and biopsy timing analyses. They will be advised on resuming their ART at home and will be followed for safety.

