#### Resume ART phase or continue ART phase

Participants who underwent ATI will continue weekly visits after ART restart, and will undergo a third and final set of imaging and sample collection within 21 days after achieving viral suppression (HIV RNA < 40 copies/mL) to facilitate understanding of what increased SUV represents (viral activity, generalized inflammation, or another process). The blinded biopsy reviewer will again determine what sites to biopsy on the basis of the whole body PET/CT images. Participants will also have the option to undergo additional lymph node biopsies on ART restart days 0, 5, and/or 10, if the lymph nodes are superficial and easily accessible for biopsy, as determined by the radiologist. Participation in this study for the ATI group ends after the third imaging visit. Supplementary Table S2 summarizes the schedule of events for ATI participants.

Participants who remained on ART will have a second and final set of imaging and lymph node biopsies at 12–16 weeks after the first, which is anticipated to correspond with the final imaging and sample collection of the ATI group. As with the ATI group, the blinded biopsy reviewer will determine what sites to biopsy on the basis of the whole body PET/CT images. Participation in this study ends after this visit. A third set of imaging and biopsies will not be pursued for those who remained on ART, because changes in PET or biopsy findings are unlikely and would be unnecessary procedures. Supplementary Table S3 summarizes the schedule of events for participants who continue ART.

After these initial 12 participants complete the study, an NIH Clinical Center (CC) staff radiologist on the study team will act as a blinded imaging reader to review the whole body PET/CT results and attempt to identify whether the participant continued their ART regimen or was on ATI. This is a different person from the blinded biopsy reviewer. The blinded imaging reviewer's success rate, and the data analysis described below, will determine if the study should be repeated to optimize timing of imaging and biopsy. A routine clinical read of the whole body PET/CT scans will also be performed by a CC staff radiologist unaffiliated with the protocol who is not blinded, and actionable results provided to the participant and/or care providers.

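### As worded, the ART restart rule keeps an ATI participant who becomes pregnant in a pathway of further research PET/CT and required lymph node biopsy

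*Protocol article*

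**What the plan says.** All references are to the protocol article.

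- *Criteria to restart ART* opens: "Participants assigned to ATI will resume ART and continue the study if they meet any of the following criteria during the ATI phase". The list includes "Participant becomes pregnant", with no qualifier. The last item reads: "Participants who are in the ATI period who trigger a withdrawal criterion (Supplementary material S2) will also resume their pre-study ART regimen".
- *Resume ART phase or continue ART phase* says what follows in this arm. After restart there are weekly visits, and participants "will undergo a third and final set of imaging and sample collection within 21 days after achieving viral suppression". The section adds: "Participation in this study for the ATI group ends after the third imaging visit".
- The Figure 1 legend gives the total: "ATI participants will undergo a total of three PET/CTs with biopsy".
- Table 2 gives the status of the biopsy: "Lymph node biopsy is required, bone marrow biopsy is optional".
- *ATI or continue ART phase* places an earlier set inside the interruption: "ATI participants will have a second set of imaging and biospecimen collection", at 7–13 days after ART is stopped.
- *Baseline/First imaging visit* gives about 2–5 biopsies after each scan.
- Pregnancy appears in three other places. It is an exclusion criterion. The *Ethics statement* repeats that exclusion and says that individual participants do not benefit. The inclusion criteria require barrier contraception or abstinence through the interruption and until re-suppression, partly to avoid pregnancy.

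**The concern.** The protocol foresees that a participant may become pregnant during the interruption and attaches an instruction to that event. Restarting ART is plainly right. The second half of the instruction, that she continues the study, is the difficulty, because in this arm the remaining study content is chiefly FDG-PET/CT and tissue sampling. The exclusion criteria also show that IV contrast, midazolam and fentanyl are anticipated.

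Pregnant women are kept out at entry of a study that offers participants no benefit of their own. A rule that, read as written, leads a participant known to be pregnant into the same procedures works against the purpose of that exclusion. At stake is the safety of any such participant. A secondary question is whether she would be replaced in an arm of six.

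**Working it through.** The main check is textual: follow an ATI participant whose pregnancy is recognised during the interruption.

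1. **Restart.** Pregnancy is a listed criterion, so she resumes ART. The lead-in attaches continuation in the study to every listed criterion.
2. **What continuing contains.** After restart: weekly visits, then the third imaging and sampling set once suppression is re-achieved. Participation ends only after that visit. The Figure 1 legend counts three scans with biopsy, and Table 2 makes the lymph node biopsy a requirement.
3. **Timing.** If pregnancy is recognised before the second set at days 7–13, that set also lies ahead. This step is slightly less firm than step 2: the text does not waive the second set when ART restarts early, but it does not discuss that case either.
4. **Exceptions.** The shown text neither exempts a pregnant participant from imaging or biopsy nor withdraws her. The contraception requirement lowers the chance of the event but gives no rule for when it occurs.
5. **Withdrawal.** Withdrawal triggers are a separate last item pointing to Supplementary material S2. Pregnancy is listed apart from that item.

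**Size per affected ATI participant** (three planned scans, about 2–5 biopsies each):

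- Recognised after scan 2: 1/3 = 33% of planned scans remain; 1 × (2 to 5) = about 2–5 biopsies.
- Recognised before scan 2: 2/3 = 67% remain; 2 × (2 to 5) = about 4–10 biopsies.

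The number of participants who could become pregnant is not given, so no trial-level frequency can be calculated.

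**Replacement.** *ATI or continue ART phase* replaces two groups: those who miss the ART restart visit, and those who withdraw before reaching a resumption criterion. Pregnancy is itself a resumption criterion, so a participant who stops because of it, and who attends the restart visit, falls clearly into neither group.

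**Cost of stopping her imaging.** These figures price the fix; they do not show a fault in the plan. The blinded reader's test uses the first two scans and a one-sided Fisher exact test. One error is taken as one swapped pair, which reproduces both of the article's figures:

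- 6 v 6: [C(6,5)·C(6,1) + 1]/C(12,6) = 37/924 = 0.040. The article states 0.04.
- 5 v 5: [C(5,4)·C(5,1) + 1]/C(10,5) = 26/252 = 0.103. The article states 0.103.

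If one ATI participant is lost before scan 2 and not replaced:

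- 5 v 6, one swap: [C(5,4)·C(6,1) + 1]/C(11,5) = 31/462 = 0.067.
- 5 v 6, all correct: 1/462 = 0.002.

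If she stops after scan 2, the reader test and the timing rule keep their data, and 1/6 = 17% of the arm's third-scan data sets is lost.

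**The case against.** The strongest objection is that the deciding text is not visible. Withdrawal criteria are in Supplementary material S2 and the ATI visit schedule is in Supplementary Table S2. A pregnancy withdrawal rule, or a pregnancy test before each scan, would normally sit in such documents, and an article may leave it there. This stands against any claim about what the full protocol does. A reader might infer that the trial would scan and biopsy a pregnant participant; the shown text does not establish that.

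Second, the lead-in cannot be literal for every item. The withdrawal item sits beneath it too, and withdrawn participants presumably do not carry on as scheduled. The section's purpose is to say when ART restarts, and a participant could meet both a restart and a withdrawal criterion. This is fair and lowers the weight of the point, but it does not remove it. If the supplement withdraws her, the lead-in says the opposite for this item; if it is silent, the lead-in is the only instruction there is.

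Third, the contraception requirement, the close safety monitoring described in the *Ethics statement*, and the ethics review all reduce the risk. That is true, but none of them says what happens once pregnancy is known.

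Fourth, the exclusion of pregnant women is an entry condition, so there is no literal contradiction with the restart list. This also stands. The conflict is with the purpose of the exclusion, not with its words.

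Finally, the 5 v 6 result arises only if imaging is stopped before scan 2, no replacement is made and the reader errs. It should carry no weight in judging the present text.

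**Conclusion.** The point holds for the wording of the article. A stated rule, not mere silence, keeps a participant who becomes pregnant in a pathway with 1 of 3 research scans and about 2–5 biopsies still ahead, or 2 of 3 and about 4–10 if recognised before the second set.

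This rests on reading continuation as the arm's general pathway, and on the shown text alone. It does not support two stronger readings: that the full protocol would image a pregnant participant, since the unseen supplements may prevent it; or that the article literally contradicts its exclusion criteria, since those govern entry. No frequency is claimed, and no defect in the reader test is alleged. The event may be rare, but the correction is short and concerns participant safety, so it is worth making.

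**What to change.** Take pregnancy out of the list governed by the continuation lead-in in *Criteria to restart ART* and give it its own sentence. For example: an ATI participant who becomes pregnant restarts ART, has no further research PET/CT or biopsy, and remains in safety and blood follow-up only. Align this with Supplementary material S2 and the schedule in Supplementary Table S2.

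In *ATI or continue ART phase*, add that she is replaced if this happens before the second scan.

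The cost is protocol and consent wording, plus the later imaging and biopsy data of that participant. After scan 2 that is 1 of 6 third-scan data sets in the arm (17%). Before scan 2, replacement restores 6 v 6, and with it the tolerance for one reader error, for one extra enrolment.

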### Analytic treatment interruption

Treatment interruptions have been studied over the last 15 years and have contributed significantly to understanding ART and HIV pathogenesis. Early studies demonstrated that cure from HIV is not possible with ART alone, and few patients maintain suppressed viral RNA levels following treatment interruption. Viral RNA levels are typically detectable within 2–4 weeks after ATI. During this early rebound period, viral RNA levels may rebound higher than viral set points prior to initial therapy, but with time off therapy, stable levels of viral RNA that are comparable to pre-therapy RNA are achieved. Shortly after treatment interruption, CD4 cell numbers may remain stable or decline slightly. New opportunistic infections are not an early consequence of treatment interruption (2–12 weeks post-interruption). The emergence of HIV drug resistance is not a typical consequence of discontinuing antiretroviral drugs (ARVs) with similar half-lives. In discontinuing regimens consisting of drugs with dissimilar half-lives [such as regimens containing non-nucleoside reverse transcriptase inhibitors (NNRTIs), which have half-lives more than 10-fold longer than nucleoside reverse transcriptase inhibitors (NRTIs) or protease inhibitors], there is a risk of emergence of NNRTI drug resistance due to the prolonged low level of NNRTI. Prolonged discontinuation from ART is associated with persistent viremia as well as progressive CD4 lymphopenia and disease progression. With the appropriate safeguards and patient counseling, ATI studies can be carried out without complications of drug resistance or HIV disease progression (56–64).

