## Methods and analysis

### Study design

This is a single-site randomized trial of the effects of ATI in six adult participants with HIV who are virally suppressed compared to six adult participants with HIV who are virally suppressed and who do not undergo ATI. Participants will be randomized 1:1 to either ATI or to continue their ART. Neither the participants nor the study team will be blinded, except for an imaging reader and biopsy reader, as described below. The study schema is shown in Figure 1. The schedule of events for participants randomized to ATI or to continue ART are shown in Supplementary Tables S2, S3.

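### The first ART restart criterion gives its absolute CD4 limit per mL instead of per μL, so that limb cannot act as written

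*Protocol article*

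**What the plan says.** Under Criteria to restart ART, the first criterion applies when HIV RNA exceeds 40 copies/mL and one of two CD4 conditions is met: "either a confirmed >30% decline in baseline CD4 cell count or an absolute CD4 count <300 cells/mL". The absolute condition reads in full: "an absolute CD4 count <300 cells/mL on 2 consecutive assesements within 2 weeks".

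Under Inclusion criteria, the entry requirement is "CD4 cell count ≥350 cell/μL".

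The rule is applied at weekly visits. The ATI section states: "HIV plasma viral levels and CD4 counts will be monitored every week during the ATI phase".

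The remaining restart triggers are:
- HIV RNA above 1,000 copies/mL sustained for at least 4 weeks
- HIV RNA above 100,000 copies/mL
- HIV-related symptoms or acute retroviral syndrome
- HIV-specific opportunistic infection
- ART needed for causes not related to HIV
- pregnancy
- 90 days off ART

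In addition, those who "trigger a withdrawal criterion (Supplementary material S2) will also resume their pre-study ART regimen". That supplement is not shown. Nothing in the article restates the absolute CD4 limit or corrects its unit.

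**The concern.** The entry floor and the restart limit describe the same measurement, but their printed units differ by a factor of 1,000. A limit of 300 per μL sits sensibly just below an entry floor of 350 per μL. A limit of 300 per mL is 0.3 per μL, which has no clinical meaning.

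The criterion exists to get participants back on ART when CD4 falls during a voluntary interruption. Its absolute limb matters for those who enter with the lowest counts, because they can drop below 300 cells/μL before losing 30% of baseline. As printed, that limb gives them nothing. The article also allows the study to be repeated with new participants, so the text may be used again.

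**Working it through.** **Inputs.** Printed absolute limit: 300 cells/mL (Criteria to restart ART). Relative limit: a decline of more than 30%, so the threshold is 0.7 × baseline B (same criterion). Entry floor: 350 cells/μL (Inclusion criteria). Monitoring: weekly (ATI section).

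**Unit conversion** (1 mL = 1,000 μL).
- As printed: 300 cells/mL ÷ 1,000 = 0.3 cells/μL.
- Evident intent: 300 cells/μL × 1,000 = 300,000 cells/mL.
- Entry floor against printed limit: 350 ÷ 0.3 ≈ 1,167.
- Fall needed from 350 cells/μL to reach the printed limit: 1 − 0.3/350 = 99.91%. To reach 300 cells/μL: 1 − 300/350 = 14.3%.

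**When the absolute limb acts first.** It does so when the absolute limit exceeds 0.7B, that is, when B is below limit ÷ 0.7.
- As printed: 0.3 ÷ 0.7 = 0.43 cells/μL, so never for an eligible participant.
- With μL: 300 ÷ 0.7 = 428.6 cells/μL, so for baselines from 350 to about 428.

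**Size on the literal reading.** The effective CD4 threshold is 0.7B instead of the larger of 300 and 0.7B (all in cells/μL):

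| Baseline B | Literal: 0.7B | Intended: max(300, 0.7B) | Difference |
|---|---|---|---|
| 350 | 245 | 300 | 55 |
| 375 | 262.5 | 300 | 37.5 |
| 400 | 280 | 300 | 20 |
| 428 | 299.6 | 300 | 0.4 |
| 428.6 and above | 0.7B | 0.7B | 0 |

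This assumes the baseline count is itself at or above 350. The article requires that for entry but does not say it of the baseline measurement.

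**Bound on delay, literal reading only.** The article says "Viral RNA levels are typically detectable within 2–4 weeks after ATI". Assume RNA is first detected at week 2 or week 4, that the first CD4 count below 300 cells/μL falls at that same visit, and that it is confirmed one weekly visit later. Assume also that CD4 stays at or above 70% of baseline.
- The intended absolute limb would be met at week 2 + 1 = 3 or 4 + 1 = 5.
- If RNA exceeds 1,000 copies/mL from first detection, the sustained-RNA rule is met at week 2 + 4 = 6 or 4 + 4 = 8. The gap is 3 weeks in either case.
- If RNA stays between 40 and 1,000 copies/mL throughout, the 90-day cap applies: 90 ÷ 7 = 12.9 weeks, a gap of 9.9 or 7.9 weeks.

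Any other trigger that acts sooner shortens these gaps.

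**The case against.** The strongest reply is that nobody would be misled. A CD4 limit of 0.3 cells/μL cannot be used, the entry criterion shows the intended unit, and "This is a single-site randomized trial", so one experienced team applies the rule. That stands, and it is why the practical risk is small.

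A second reply is that this is a journal article condensing a full protocol that is not shown. The article has other slips, including a misspelling in the same sentence, so the error may be confined to it. That is possible and cannot be settled from the article. It is a reason to check the full protocol. It does not make the printed criterion right. Nor is this detail left to another document: the threshold is stated here, and it is stated wrongly. A text-extraction fault is unlikely, since the μ came through intact in the inclusion criteria.

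A third reply is that the delay scenarios are improbable. They need literal application, one of only six ATI participants with a baseline in the affected range, and a CD4 count that falls below 300 cells/μL but not below 70% of baseline. The longest also needs RNA to stay low until day 90. The article's own account of interruption, in which early CD4 counts hold or dip slightly and RNA may overshoot its earlier set point, suggests the viral-load triggers would usually act first. This also stands. The week figures are outer bounds and not expectations. The trigger for medically necessary ART is also limited to causes not related to HIV, so it should not be counted as protection against HIV-related CD4 loss.

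**Conclusion.** The concern holds. The printed absolute CD4 limit is too low by a factor of 1,000, and as written that limb is redundant for every eligible participant. With the evident unit it would be the earlier CD4 trigger for baselines from 350 to about 428 cells/μL. On the literal reading the loss is at most 55 cells/μL in the threshold. Under the stated assumptions the delay is about 3 weeks when RNA exceeds 1,000 copies/mL from detection, and at most about 8 to 10 weeks when RNA stays between 40 and 1,000 copies/mL.

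These sizes apply only if staff follow the text literally, which is unlikely. This is a correction to the text of a safety rule and not a flaw in the design. It should be made because the rule governs when participants go back on treatment.

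**What to change.** In the first restart criterion, change the unit of the absolute CD4 limit from cells/mL to cells/μL, so that it reads below 300 cells/μL and matches the inclusion criterion. Confirm that the full protocol in use at the site carries the same unit. No other restart criterion needs to change for this point. The cost is one unit in the text and one check, with no effect on sample size, visits or analysis.
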